### Study design

2.1.

The present study will be conducted as an assessor-blinded, randomized, controlled trial with a crossover design at a rehabilitation hospital. Participants will be randomly allocated to either the treatment sequence: VR-MAT first and second with conventional cognitive training (CT) (VC group), or in the opposite order (CV group) with an allocation ratio of 1:1 using a computer-generated randomization table. The crossover design is selected because the participants need to serve as their own control group to minimize confounding effects on cognition, which might be markedly affected by a person’s traits, which is not intended by the intervention. In addition, it might be beneficial for the statistical efficiency of this pilot trial, in which VR-MAT had not been attempted for patients with ABI.

Each VR-MAT or CT training period will last 4 weeks with five 30-min intervention sessions per week, resulting in a total of 20 sessions. Therefore, each participant will have received a total of 40 sessions of the intervention, comprising 20 sessions of VR-MAT and 20 sessions of CT. The randomized group assignments were concealed in consecutively numbered sealed opaque envelopes placed in a plastic container. The allocated group will then be determined by the sequential opening of the envelopes after obtaining written informed consent from the participants. Participants will receive a conventional inpatient rehabilitation program (1 h of physical therapy or 30 min of occupational therapy); however, they will not receive a cognitive intervention. Outcome measurements will be performed by a researcher blinded to the group assignment.

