### Participants

2.2.

Participants will be recruited among patients who have been admitted to the neurorehabilitation unit of the rehabilitation hospital. The inclusion criteria are as follows: (1) cognitive impairment secondary to a first-ever ABI, as evidenced by a Clinical Dementia Scale (CDR) score of 0.5 – 1; (2) a diagnosis of ABI > 3 months ago with medical records and/or brain imaging; (3) no history of prior ABI; (4) upper limb muscle strength of ≥ 3 on the medical research council scale, indicating suitability for training and assessment; (5) age >19 years. The exclusion criteria are: (1) known cognitive impairment prior to ABI; (2) severe aphasia or cognitive communication disorder precluding cognitive intervention, including MAT and CCT, or assessment; (3) neurological or psychiatric disorders other than ABI; (4) severe depression (Geriatric Depression Scale-short form score of ≥8); (5) uncontrolled medical illnesses, such as severe cardiac or respiratory disease. The exclusion criteria are as follows: (1) known cognitive impairment prior to ABI; (2) severe aphasia or cognitive communication disorder which precluded cognitive intervention including MAT and CCT or assessment; (3) neurological or psychiatric disorder other than ABI; (4) severe depression [Geriatric Depression Scale-short form ≥8]; (5) uncontrolled medical illness such as severe cardiac or respiratory disease. The experimental protocol was approved by the ethics committee of the rehabilitation hospital (IRB no. NRC-2015-04-032). Sample size calculation was not possible because the effects of the VR-MAT on cognitive function have not yet been reported. Therefore, we have set the sample size to 12 for each arm, in accordance with the minimum number recommended for pilot trials (46, 47). In total, considering a potential participant attrition rate of 20%, we aim to recruit 24 participants for this pilot study.

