### Outcome measurement

2.5.

Baseline demographic characteristics, including sex, age, diagnosis of ABI, duration after ABI, side of brain lesion, and education, will be collected. Additionally, neuropsychological outcomes will be measured for each participant at baseline, after 20 sessions (4 weeks), and after 40 sessions of intervention (after 20 sessions of alternative intervention; 8 weeks) by a blinded neuropsychologist. We will collect data on neuropsychological outcomes in two ways: global cognitive function and executive function, which are specific targets of VR-MAT. All of the cognitive function tests will be administered in Korean. Additionally, we will obtain VR-MAT behavioral data, which is previously explained, and functional infrared spectroscopy (fNIRS) data (Table 1).

**Table 1 tab1:** List of outcome measurements.

Global neuropsychological assessment	Mini-mental status examination (MMSE)
Clinical dementia rating (CDR)
Global deterioration scale (GDS)
Subjective memory complaint questionnaires (SMCQ)
Executive function assessment	Trail making test (TMT)
	TMT-black & white (TMT-B&W)
	Attention-switching Task (AST)
	Stop signal task (SST)
	Spatial working memory (SWM)
VR-MAT behavioral measures	VR-MAT response time
	VR-MAT accuracy
Functional near-infrared spectroscopy	Oxygenated hemoglobin
	Deoxygenated hemoglobin
	Total hemoglobin concentration
	Oxygen level change

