### Statistical analysis

2.7.

We will perform descriptive statistical analysis of the general demographics of the study participants. We define completers as participants who finish 20 sessions of either intervention (VR-MAT or CT) and undergo measurements at 4 weeks of intervention. The statistical analysis will be conducted on an intention to treat basis and the last observation carried forward method will be used to complete the data. Adherence will be reported as the number of completers among enrolled participants. For neuropsychological assessments, a comparative analysis between two different intervention sequences (VC or CV) will be performed and the carry-over effects will be tested using *t*-tests on the change in each sequence for all crossover endpoints (70, 71). For variables with insignificant carry-over effects, the changes in variables during specific interventions from either sequence will be combined and compared. For patients with significant carry-over effects, we will compare the changes in specific interventions during the first period (20 sessions of either intervention). Comparisons between interventions will be performed using a two-tailed *t*-test or the Mann–Whitney *U* test, depending on normality. For music behavior responses obtained from the VR-MAT data, we will perform a two-way repeated-measures analysis of variance (ANOVA) on level (levels 1, 2, 3, and 4) and time (pre, day 8, day 15, and post) with Bonferroni *post-hoc* comparisons.

Repeated measures of correlation between executive function assessment and VR-MAT variables will be examined to determine the linear relationship between paired repeated data using the R package rmcorr from R.3.6.1 (72). The independent variables will remain the same for the analysis of fNIRS data, and the dependent variables will be the PRIs obtained from all channels. All analyses will be performed using the software package R.3.6.1,^1^ and the level of significance will be set to 0.05.

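### Carrying the last observation forward sets dropouts' within-period change to exactly zero, which can distort the crossover comparison and makes its interval too narrow

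*Protocol article*

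**What the plan says.** All of this is in the protocol article.

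- **Missing data** (Statistical analysis): the analysis is by intention to treat, and "the last observation carried forward method will be used to complete the data".
- **Assessments** (Outcome measurement): neuropsychological outcomes are taken "at baseline, after 20 sessions (4 weeks), and after 40 sessions of intervention". There is one assessment at the end of each period and none within a period.
- **Periods** (Study design): "Each VR-MAT or CT training period will last 4 weeks with five 30-min intervention sessions per week". Two such periods fill weeks 0 to 8, and no washout or second baseline is described. The week-4 score therefore ends period 1 and starts period 2.
- **Analysed quantity** (Statistical analysis): where carry-over is not significant, "the changes in variables during specific interventions from either sequence will be combined and compared". Where it is significant, "we will compare the changes in specific interventions during the first period (20 sessions of either intervention").
- **Test** (Statistical analysis): "Comparisons between interventions will be performed using a two-tailed" t-test or a Mann–Whitney test, and "the level of significance will be set to 0.05".
- **Expected loss** (Participants): 24 are to be recruited, "considering a potential participant attrition rate of 20" per cent.

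**The concern.** The endpoint is a change between two adjacent visits. If the later visit is missing and the earlier score is copied into it, the change is zero by construction. There is no within-period score that could be carried forward instead.

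Zero is a neutral value only if the average change is zero. The article gives no expected change. It does describe the control as active training modelled on an effective method, continues inpatient rehabilitation throughout, and repeats the same tests three times, so average improvement is plausible. It remains an assumption. If it holds, each filled-in zero pulls an intervention's mean towards no change, and how far depends on who leaves and when. The zeros are then analysed as if they had been measured.

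At stake are the effect estimate and its interval, which a later trial would draw on because the article reports no earlier estimate for VR-MAT.

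**Working it through.** **Inputs.** From the article: 12 per sequence, 24 in total, 20% attrition, three visits, two periods. Assumed because the article gives none: SD of a within-period change = 1, mean changes of 0 to 1 SD, dropout unrelated to the scores. For timed tests, read improvement as a fall; the argument is the same.

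**Step 1: how many zeros.** 24 × 0.20 = 4.8 participants leave and 19.2 stay. There are 24 × 2 = 48 within-period changes.
- All leave in period 2: 4.8 / 48 = 10% of changes are zeros.
- All leave in period 1: 9.6 / 48 = 20% are zeros.

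**Step 2: what is carried.**
- Leaves in period 2: week 8 := week 4, so the second change is 0 and the real first change is kept.
- Leaves in period 1: week 4 and week 8 := baseline, so both changes are 0.

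**Step 3: effect on the difference.** Let a be the dropout probability during VR-MAT and b during conventional training (CT). The share of real changes kept is
- pooled: VR-MAT (1 − a)(1 − b/2), CT (1 − b)(1 − a/2);
- first period only: VR-MAT 1 − a, CT 1 − b.

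Each mean change is multiplied by its kept share. A simulation with 12 per sequence and 6,000 runs per row gave the values in brackets.

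| Mean change VR-MAT / CT (SD) | a / b | True difference | Pooled | First period |
|---|---|---|---|---|
| 0.5 / 0.5 | 10% / 10% | 0 | 0 (-0.001) | 0 (0.005) |
| 0.5 / 0.5 | 20% / 0 | 0 | 0.40 − 0.45 = -0.05 (-0.053) | 0.40 − 0.50 = -0.10 (-0.110) |
| 1.0 / 1.0 | 20% / 0 | 0 | 0.80 − 0.90 = -0.10 (-0.103) | 0.80 − 1.00 = -0.20 (-0.210) |
| 0.8 / 0.3 | 10% / 10% | 0.50 | 0.855 × 0.50 = 0.43 (0.425) | 0.90 × 0.50 = 0.45 (0.451) |
| 0.8 / 0.3 | 20% / 0 | 0.50 | 0.64 − 0.27 = 0.37 (0.374) | 0.64 − 0.30 = 0.34 (0.341) |
| 0.8 / 0.3 | 0 / 20% | 0.50 | 0.72 − 0.24 = 0.48 (0.480) | 0.80 − 0.24 = 0.56 (0.561) |

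Now let the gain differ by period: no treatment difference, 0.5 SD in period 1, 0.3 SD in period 2, and 20% dropout on VR-MAT only.
- VR-MAT: (0.8 × 0.5 + 0.8 × 0.3) / 2 = 0.32.
- CT: (0.5 + 0.8 × 0.3) / 2 = 0.37.
- Pooled difference: 0.32 − 0.37 = -0.05 SD.
- First-period difference: 0.40 − 0.50 = -0.10 SD.

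**Step 4: effect on the standard error.** If a share d of changes is set to 0 and the rest have mean μ and SD 1, the variance is (1 − d)(1 + dμ²). Dividing the resulting SE by the SE from observed changes alone gives (1 − d)√(1 + dμ²).
- d = 0.10: 0.90 at μ = 0, and 0.90 × √1.1 = 0.944 at μ = 1.
- d = 0.20: 0.80 at μ = 0, and 0.80 × √1.2 = 0.876 at μ = 1.

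The SE is therefore about 6–20% smaller than the observed data give.

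**Step 5: false positives.** With no true difference and 20% dropout in one intervention only, the simulated type I error was 5.2–5.5% for the pooled t-test and 6–9% for the first-period test. With 10% dropout in each, the pooled test gave 4.4%. Analysing observed changes only showed no bias in any row (-0.004 to 0.003 for a true 0; 0.497 to 0.504 for a true 0.50), as expected when dropout is unrelated to the scores.

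**The case against.** The other side has several fair points.

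- **The bias is conditional.** With equal true changes and equal dropout the difference is unbiased. Nothing in the article suggests that dropout will differ between the interventions. This stands.
- **The distortion is small beside the noise.** A spurious 0.05 SD is about a fifth of the simulated SE of 0.27. With equal dropout the effect is attenuation, which does not favour VR-MAT. This stands too, although the first-period analysis doubles the distortion.
- **It is a pilot with no efficacy sample size.** True, but the article still tests at the 0.05 level and sets out to evaluate efficacy, so the estimate and interval will be read.
- **Intention to treat calls for complete data.** It does not. It fixes who is analysed and in which group, and does not require single imputation.
- **An article condenses a fuller plan.** Extra sensitivity analyses may exist elsewhere. The point does not rest on their absence: carry-forward is stated here as the method.

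Two stronger readings are tempting. A reader might infer from √(19.2/24) = 0.894 that the SE is understated by at least 11%. That treats every leaver as contributing nothing, whereas a period-2 leaver keeps a real first change, so the understatement can be as low as about 6%. A reader might also infer that too small an SE means many false positives. The pooled simulations do not show this. The computed SE matched the actual spread of the carried-forward estimate (0.269 against 0.269 in the second row of the table); it is the precision of a diluted quantity, not of the real within-period change.

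**Conclusion.** The point holds in a conditional form. Given the visit schedule, the stated rule turns a missing visit into a change of exactly zero and counts it as observed; that much follows from the article alone. Whether it biases the comparison depends on two things the article does not give: that scores change on average, and either that the interventions truly differ or that dropout differs between them.

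Under the assumed values, a true difference of 0.50 SD became 0.37 to 0.48 SD pooled and 0.34 to 0.56 SD in the first-period analysis. A true difference of zero became 0.05 to 0.10 SD pooled and 0.10 to 0.20 SD in the first period when 20% left one intervention only. The main harm is a distorted estimate with too narrow an interval, not a materially higher false-positive rate in the pooled test.

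The article does not support reading this as bias in favour of VR-MAT, or as certain bias. The zero-change argument covers the neuropsychological crossover endpoints. VR-MAT performance is measured four times, and there the rule freezes a participant's curve at its last value instead.

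**What to change.** Remove carry-forward as the main method.

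- Analyse all randomised participants with any observed score in a likelihood-based mixed model of the baseline, week-4 and week-8 scores, with treatment and period terms and a small-sample degrees-of-freedom correction. This is valid under missing at random and needs no imputation.
- For ordinal ratings (such as the CDR and the Global Deterioration Scale) or clearly non-normal endpoints, apply the planned rank test to observed changes only. State that this relies on dropout being unrelated to the change.
- If carry-forward is kept, show it only as a sensitivity analysis.

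**Cost:** the mixed model replaces the planned t-test for endpoints suited to it, so this is more than a change of wording, but the programming is modest and R is already in use. Intervals will be wider: by 1/0.944 to 1/0.90, or about 6–11%, where 10% of changes are missing, and by 1/0.876 to 1/0.80, or about 14–25%, where 20% are. These figures come from the observed-change comparison in Step 4. The extra width reflects information the trial does not have.

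### The pooled crossover comparison in section 2.7 reads as an unpaired test although every participant is in both groups, so its standard error is wrong except by coincidence

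*Protocol article*

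**What the plan says.** Section 2.7 first tests carry-over for each crossover endpoint. Where it is not significant, "the changes in variables during specific interventions from either sequence will be combined and compared". Where it is significant, only first-period changes are compared. One sentence gives the test for both routes: a "two-tailed *t*-test or the Mann–Whitney *U* test, depending on normality". All analyses share one threshold: "the level of significance will be set to 0.05".

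Three facts from elsewhere in the article bear on this:
- Section 2.1: "each participant will have received a total of 40 sessions of the intervention, comprising 20 sessions of VR-MAT and 20 sessions of CT". Everyone is exposed to both interventions.
- Section 2.1 justifies the crossover because "the participants need to serve as their own control group to minimize confounding effects on cognition", and also on grounds of statistical efficiency.
- Section 2.5: neuropsychological outcomes are measured "at baseline, after 20 sessions (4 weeks), and after 40 sessions of intervention". There are three scores per person and hence two consecutive changes.

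**The concern.** Pooling by intervention forms a VR-MAT group of changes and a CT group of changes that contain the same people. A test for independent samples assumes that the two means vary independently. Here they do not: an unusually high week-4 score raises the first change and lowers the second, while a person who recovers steadily has both changes raised.

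This is the route to the VR-MAT versus CT comparison for every neuropsychological endpoint that is not diverted by the carry-over test. If the two changes are negatively correlated, the standard error is too small and p-values are too optimistic. If they are positively correlated, it is too large and the efficiency that motivated the crossover is lost. In both cases the within-person control promised in section 2.1 is not used.

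**Working it through.** **Inputs from the article.** Significance level 0.05, two-tailed (section 2.7). 12 participants per sequence, 2 × 12 = 24 in total (section 2.2). Allocation 1:1 (section 2.1). Scores Y0, Y1 and Y2 at baseline, 4 and 8 weeks (section 2.5). The 0.05 is set and not derived, and no power, SD or correlation is given, so there is no further figure to reproduce. The correlations below are assumptions.

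**Step 1: standard error.** Let N participants each give two changes with variance v and correlation c. For the difference between the two intervention means, with no period effect:
- variance assumed by an unpaired test: 2v/N
- true variance: (2v/N)(1 − c)
- actual two-sided size at nominal 5%: 2[1 − Φ(1.96/√(1 − c))]

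The size is 5% only if c = 0.

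**Step 2: equal correlation r among the three visits, variance s².**
- Var(Y1 − Y0) = 2s²(1 − r)
- Cov(Y1 − Y0, Y2 − Y1) = −s²(1 − r)
- c = −0.5, whatever r is
- assumed SE / true SE = √(1/1.5) = 0.816, so the SE is 18% too small
- 1.96 × 0.816 = 1.60, giving a size of 0.1095

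**Step 3: AR(1).** The covariance is −s²(1 − r)², so c = −(1 − r)/2. For r = 0.5, 0.7 and 0.8, c = −0.25, −0.15 and −0.10, and the size is 0.080, 0.068 and 0.062.

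**Step 4: simulation under no treatment effect, 12 per sequence** (40,000 runs for t-tests, 10,000 for Mann–Whitney U). The last column is a two-sample t-test between sequences on each participant's period-1 change minus period-2 change.

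| Assumed structure | Unpaired t | Mann–Whitney U | Period differences between sequences |
|---|---|---|---|
| Equal correlation, r = 0.5 / 0.7 / 0.8 | 0.107 / 0.111 / 0.109 | 0.102 / 0.104 / 0.100 | 0.050–0.051 |
| AR(1), r = 0.5 / 0.7 / 0.8 | 0.078 / 0.067 / 0.060 | 0.077 / 0.064 / 0.057 | 0.049–0.051 |
| Equal correlation 0.7, period difference in mean change of 0.5 / 1 / 1.5 SD of change | 0.096 / 0.071 / 0.046 | 0.090 / 0.067 / 0.037 | 0.048–0.051 |
| Equal correlation 0.7 plus person-specific slopes, c = 0 / 0.25 / 0.44 | 0.050 / 0.025 / 0.012 | 0.044 / 0.025 / 0.012 | 0.048–0.050 |
| Equal correlation 0.7, 20% lost after week 4, last observation carried forward | 0.099 | 0.096 | 0.048 |

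The carry-over pre-test does not rescue the comparison. Under equal correlation the whole two-stage procedure has size 0.110–0.113.

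**Step 5: why period must be handled too.** With balanced sequences, a period effect widens the spread inside each pooled group, so it lowers the size of the unpaired test. It does the same to a simple paired t-test, whose size falls from 0.048 to 0.010 as the period difference goes from 0.25 to 1.5 SD. Comparing period differences between sequences removes the period effect.

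**Step 6: a tempting remedy that fails.** A mixed model of the two changes with only a random participant intercept cannot represent a negative correlation. Under equal correlation its participant variance was estimated at zero in 99% of simulated runs, and type I error stayed at 10.7–11.1%.

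**The case against.** The article never uses the word unpaired. The sentence beginning "Comparisons between interventions will be performed using a two-tailed" also covers the first-period analysis, where independent-samples tests are right. Section 2.7 also announces a comparison between the two sequences, and a t-test or Mann–Whitney U between sequences on within-person period differences is a valid crossover analysis. The article is condensed, and the full plan may say more. This stands in part: unpaired is a strong inference and not a stated term. But the text describes changes pooled by intervention, which is a different operation from differencing within person. Even if the t-test were meant as paired, Mann–Whitney U would still be wrong for changes pooled in that way.

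A reader might infer that the plan has an 11% false-positive rate. The documents do not support that. They give no correlation, and 11% is about the top of the range for the pooled test over the structures tried. Participants may well recover at different rates, which pushes the correlation towards or above zero.

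A reader might also infer that dropout will unbalance the sequences and let the period effect leak into the treatment contrast. Section 2.7 does not support this: analysis is by intention to treat with last observation carried forward, so dropouts stay in their sequence. Whether that imputation distorts the changes is a separate question.

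Finally, this is a pilot without a sample size calculation, and with balanced sequences the fault affects the standard error and not the point estimate. That limits the consequences. It does not make the test valid, and the Discussion looks to the results to show efficacy.

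**Conclusion.** The rule is wrong as written. As the text reads, the same participants form both groups and the test treats them as different people, so the standard error is right only if the dependence happens to be nil or is offset by something else, such as an unmodelled period effect. The direction and size cannot be fixed from the article. For the t-test with no period effect, type I error is about 11% under equal correlation and about 6–8% under AR(1) with r = 0.5–0.8. With positively correlated changes or a large unmodelled period effect it is 5% or below, and the cost is power. The conclusion that the method is unsuitable does not depend on the 11%. It does depend on reading the comparison as unpaired, which is the natural reading of the wording but not an explicit statement.

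**What to change.** In section 2.7, for endpoints analysed over both periods, state that each participant's period-1 change minus period-2 change will be computed. Compare these differences between the VC and CV sequences with a two-sample t-test, or with Mann–Whitney U if non-normal. Half the difference between the sequence means estimates the treatment effect, and the period effect cancels.

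An equivalent linear model of the changes with treatment, period and fixed participant effects may be used, or a model with an unstructured within-participant covariance. A random participant intercept alone on the changes should not be used, for the reason in step 6 of the working. Keep the unpaired comparison of changes only for the first-period analysis.

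The cost is a few sentences, with the same data and the same R software. The t-test has 22 degrees of freedom (12 + 12 − 2) where the pooled test would claim 46 (24 + 24 − 2). Some p-values will become less favourable.

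### A per-endpoint carry-over pretest on change scores, with no washout, is confounded with the treatment effect unless gains persist fully; with the unpaired pooled test it leads to, the 5% level is not held

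*Protocol article*

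**What the plan says.** All references are to the protocol article.

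- **Pretest and switch** (Statistical analysis). Carry-over is tested by t-tests on changes for every crossover endpoint. If the test is not significant: "For variables with insignificant carry-over effects, the changes in variables during specific interventions from either sequence will be combined and compared". If it is significant: "For patients with significant carry-over effects, we will compare the changes in specific interventions during the first period". The second sentence says patients where the first says variables; the sense requires variables in both.
- **Test and level** (Statistical analysis). "Comparisons between interventions will be performed using a two-tailed" t-test, or a Mann–Whitney U test if normality fails, and "the level of significance will be set to 0.05". No separate level is given for the pretest, and nothing controls the error of the two-stage choice.
- **Timing** (Study design; Outcome measurement). There are two 4-week periods, and "neuropsychological outcomes will be measured for each participant at baseline, after 20 sessions (4 weeks), and after 40 sessions of intervention". The second period ends at week 8, and 4 + 4 = 8 leaves no time for a washout or a second baseline.
- **Size** (Participants). "we have set the sample size to 12 for each arm". No effect size, SD or correlation is given, because none had been reported for this intervention.

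**The concern.** Three features combine badly.

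1. A preliminary test chooses the estimator separately for each endpoint, so two endpoints in one results table may be answering different questions.
2. Because the period-2 change starts from a week-4 score that already contains the period-1 treatment effect, a between-sequence difference in changes can reflect the treatment effect instead of carry-over.
3. When both periods are pooled, each participant contributes two correlated changes, one to each side of a test that treats all the changes as independent.

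This is the only between-intervention analysis stated for the neuropsychological endpoints. The size of the VR-MAT effect and the meaning of its p-value both depend on it.

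**Working it through.** **Inputs.** From the article: 12 per sequence, two-sided 0.05, visits at baseline, week 4 and week 8. Assumed, because the article gives none: a VR-MAT minus CT effect d; a retained fraction q of the period-1 gain at week 8; inter-visit correlation 0.7, equal for all pairs of visits; score SD 1; no period difference. The change SD is then √(2 × 0.3) = 0.775, and the two successive changes correlate (0.7 − 1)/(2 × 0.3) = −0.5.

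**Expected values.** Let tV and tC be the effects on the score, d = tV − tC, and p1, p2 the period levels.

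| Sequence | Period-1 change | Period-2 change |
|---|---|---|
| VC | tV + p1 | tC − (1 − q)tV + p2 − p1 |
| CV | tC + p1 | tV − (1 − q)tC + p2 − p1 |

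- Pooled contrast: ½[2d + (1 − q)d] = (1.5 − 0.5q)d. This is 1.5d at q = 0, 1.1d at q = 0.8 and d at q = 1.
- Summed-change pretest (week 8 minus baseline, VC minus CV): −(1 − q)d. It has mean zero only if d = 0 or q = 1.
- Period-1 contrast: d for every q.

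**The estimate the plan would report.** Simulation of the full two-stage rule with d = 0.5 SD of the score:

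| q | Pooled contrast | Reported after the switch | Bias |
|---|---|---|---|
| 0 | 0.75 | 0.61 | about +23% |
| 0.5 | 0.62 | 0.58 | about +16% |
| 0.8 | 0.55 | 0.535 | +7% |
| 1 | 0.50 | 0.50 | none |

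The pretest is significant in about 33% of trials at q = 0 and 5% at q = 1.

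**Other readings of the pretest.** The wording also allows a test of the period-2 change between sequences, or of period 1 against period 2 within a sequence. With d = 0.8 SD of change and change correlation −0.5, the share of significant pretests is:

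| Reading | q = 0 | q = 0.5 | q = 1 |
|---|---|---|---|
| Summed change | 47% | 15% | 5% |
| Period-2 change | 96% | 80% | 47% |
| Within sequence | 88% | 72% | 52% |

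**Power for real carry-over.** With no treatment effect and an additive carry-over of 0.5 SD of change in VC, the summed test is significant in about 22% of trials. The reported contrast is then biased by −0.14 SD of change, and type I error is 0.16.

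**Type I error with no effect and no carry-over.** The stated figure is 0.05. With σ² the variance of a change and ρ the correlation of a participant's two changes:

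- Variance assumed by the unpaired pooled test (24 against 24): σ²(1/24 + 1/24) = σ²/12.
- True variance of the contrast: σ²(1 − ρ)/12, which is 1.5σ²/12 at ρ = −0.5. The standard error is understated by √1.5 = 1.22.
- The critical value 2.01 acts as 2.01/1.22 = 1.64, a two-sided error of about 0.10.

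Simulation at ρ = −0.5 agrees:

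| Procedure | Type I error |
|---|---|
| Two-stage rule as written, summed pretest | 0.11 |
| Unpaired pooled test alone, no pretest | 0.11 |
| Two-stage rule, within-participant test in the pooled branch | 0.055 to 0.057 |
| Period-1 comparison alone | 0.05 |

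As written with the summed pretest, the error is 0.113, 0.087, 0.063 and 0.040 at change correlations −0.5, −0.25, 0 and +0.3. Over all three readings, and with 10 or 12 per sequence, it runs from about 0.017 to 0.113.

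**The case against.** Much of the case for leaving the rule alone deserves a hearing.

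- **Pooling bias.** A reader might infer that the reported effect is inflated by 50%. That figure is the pooled contrast at q = 0 as if the plan always pooled. On the summed reading the pretest fires more often just when pooling is biased and moves the analysis to period 1, which cuts the bias to about 23%. Training is meant to last, and with full retention there is none.
- **Cause of the error.** A reader might infer that the pretest is what breaks the 5% level. It adds about half a percentage point to one point at the assumed correlation. Given a significant summed pretest, the period-1 test rejects in 16% to 42% of null trials, but only about 5% of null trials get there.
- **What the pretest detects.** It would be too strong to say that it responds to the treatment effect and not to carry-over. The summed test does respond to additive carry-over, but weakly.
- **Ambiguity.** The pretest is described briefly with two citations, and the direction of the error depends on the reading. The pooled t-test is not expressly called unpaired; that is inferred from its pairing with the Mann–Whitney U test. A period difference such as practice would add within-group variance and lower the unpaired test's error.
- **Pilot status.** The trial is a pilot and the Discussion says effectiveness will be explored. The same section also speaks of demonstrating efficacy.

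These points limit the size and direction of the error. They do not rescue the rule, whose level and estimand depend on a retention and a correlation that nobody knows in advance.

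**Conclusion.** The point stands in a limited form. A stated rule selects the analysis per endpoint by a pretest that, without washout, cannot separate the treatment effect from carry-over unless gains persist fully, and that has little power for real carry-over. Absent additive carry-over, the bias of the reported estimate on the summed reading runs from none to about +23% as retention falls from full to nil. The nominal 5% is not guaranteed: it is about 0.11 at equicorrelated visits, mainly from the unpaired pooled test, and it can be below 5% elsewhere. The algebra needs only additive effects and a common retained fraction; the percentages rest on the assumed effect, correlation and absence of a period difference. The documents do not support a claim that the procedure is always biased or always anti-conservative.

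**What to change.** Reword the Statistical analysis section only:

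1. Delete the carry-over pretest and the per-variable switch.
2. Fix one analysis for all neuropsychological endpoints: week-4 score compared between VC and CV by ANCOVA adjusted for the baseline score. No carry-over can enter this comparison.
3. Make any two-period analysis secondary. Use a within-participant, period-adjusted test in place of the unpaired one, and state its persistence assumption. Change scores estimate (1.5 − 0.5q)d and are unbiased only under full persistence. Week-4 and week-8 scores estimate (1 − q/2)d and are unbiased only under none: at q = 1 they give 0.25 for a true 0.50.
4. Report the carry-over estimate with its confidence interval descriptively, never as a gate.

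**Cost.** The interval is wider than in a two-period analysis. At inter-visit correlation 0.7, with score variance 1:

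- ANCOVA variance: 2 × (1 − 0.49)/12 = 0.085. An unadjusted period-1 change comparison has 2 × 0.60/12 = 0.100, so baseline adjustment saves 15%.
- Two-period change analysis: 0.60 × 1.5/12 = 0.075. The ANCOVA interval is wider by a factor of √(0.085/0.075) = 1.06.
- Two-period score analysis: ¼ × 2 × 0.60/12 = 0.025. The factor is √(0.085/0.025) = 1.84, the price of not assuming that nothing persists.

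Power is modest: the unadjusted period-1 change comparison has about 0.46 for 0.8 SD of change with 12 per arm. The pilot should therefore report estimates with intervals.
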